### Statistical analysis

All data will be analyzed using R [50] and Mplus [51]. Each family will be assigned a unique study ID to ensure anonymized data handling. Statistical analyses will follow a staged approach, aligned with the study’s three hypotheses. Missing data will be handled using full information maximum likelihood estimation within Latent Change Score (LCS) and multilevel models, minimizing bias due to attrition or intermittent missingness. Sensitivity analyses, including intention-to-treat analyses that incorporate all randomized participants regardless of adherence or dropout, will be performed to assess the robustness of the findings. Additional subgroup analyses exploring moderators such as child age, gender, and baseline severity will be conducted to evaluate consistency of intervention effects.

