## Materials and methods

### Study design

This protocol, which adheres to the SPIRIT 2013 guidelines (see S1 File), describes the Dino Study (Daily Intervention-based research on Nurturing Opportunities), a two-arm randomized controlled trial (RCT) designed to evaluate the effectiveness of the IY Small Group Dinosaur Child Program in Dutch children aged 4–8 years with perceived elevated or (sub)clinical levels of conduct problems [20,21,24]. A total of 120 children and one primary caregiver per family will be enrolled and randomly assigned to either an intervention group (n = 60) or a waitlist control group (n = 60), using a 1:1 ratio. The study assesses both group-level effects and individual variability in treatment response by analyzing intensive longitudinal data (ILD) from daily diaries to capture children’s moment-to-moment negative affect, externalizing behaviors, and daily parent–child interactions. The intervention group will receive the Dinosaur Child Program in small groups across 18 weekly sessions. The control group will receive care-as-usual and will be offered the intervention after posttest assessment. Pretest (T1) and posttest (T2) assessments will be conducted using standardized questionnaires and a brief child interview, with T2 scheduled 19 weeks after T1. In addition, daily diary data on children’s emotional states, behavior problems, and parent–child interactions will be collected via the m-Path application [26] during a one-week baseline period, the 18-week intervention, and a one-week follow-up (i.e., 20 weeks total). Parent and child will complete the diary jointly each evening (Fig 1). Eligibility criteria include: (a) child age between 4 and 8 years at the start of the study (September 2025), (b) parental indication that the child shows elevated or (sub)clinical levels of conduct problems in daily life (e.g., frequent defiance, aggression, or rule-breaking behavior), (c) daily contact between the child and the participating parent, and (c) sufficient fluency in Dutch. Children are excluded if they have an intellectual disability (IQ < 70) or insufficient Dutch language proficiency.

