### Recruitment

Participants will be recruited from primary schools as well as preventive and clinical settings in collaboration with two mental health institutions. Information will be shared via email, school newsletters, posters, and individual consultations. Schools previously engaged in the IY training network will be prioritized. Parents who express interest will complete an online registration form and subsequently participate in a video call with trained research staff, who will confirm eligibility and provide detailed information about the study. During this call, digital informed consent will be obtained from parents or legal guardians. When appropriate, children will accompany this call and be given age-appropriate information and asked to provide verbal or digital assent. Participants will have the opportunity to ask questions and may withdraw from the study at any time without consequence.

Approximately one month prior to the intervention, families will receive a home visit to establish rapport and conduct baseline procedures. In the intervention group, this visit will be conducted by the child’s future group leader; in the control group, by a trained research assistant. During the visit, children will provide oral assent and complete a brief, age-appropriate interview. Parents will complete baseline questionnaires and receive instructions for installing the m-Path app [26]. An overview of participant flow, including enrollment, randomization, and assessment timing, is shown in Fig 2.

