#### Preliminary analyses.

To evaluate baseline equivalence between the intervention and control groups, independent samples t-tests (or Mann–Whitney U tests for non-normally distributed variables) will be conducted on demographic characteristics, baseline parenting behavior, and child behavioral outcomes. Any baseline differences that reach statistical significance will be included as covariates in subsequent models.

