#### Hypothesis 1: Group-level behavioral effects.

To assess whether participation in the Dinosaur Child Program leads to greater improvements in children’s emotional, social, behavioral and cognitive functioning, LCS models will be estimated in Mplus for each primary outcome domain: child externalizing behavior, social competence, emotional understanding, and cognitive functioning. Outcomes will be analyzed separately for parent-reported, teacher-reported, and child-assessed measures. LCS models estimate change over time using latent difference scores, thereby distinguishing true change from measurement error. Intervention condition will be tested as a predictor of pre-to-post change examine differential improvements between the intervention and control group. Each latent change score model will estimate the average change over time, interindividual variability in change, and the effect of group assignment on these change scores. Bonferroni-adjusted significance thresholds will be applied to control for multiple comparisons across outcome domains.

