Another important contribution of this study is its focus on affective parent–child dynamics as both an outcome and potential mechanism of change. Rather than limiting evaluation to child behavior alone, daily surveying will provide insights into shared emotional experiences and daily escalation or co-regulation patterns. This level of resolution allows researchers to move beyond the “omnibus effect” typically reported in large-scale RCTs and begin unpacking the micro-level processes that may underlie successful behavior change. At the same time, the study acknowledges the inherent complexity of such data: the intervention is a multi-component program, and causal specificity regarding which elements are most effective may remain difficult to determine.

The waitlist control design allows for strong internal comparisons, but it does not isolate non-specific intervention effects such as increased attention or structure. Furthermore, although the ILD approach is developmentally adapted and only administered once daily, the potential burden on families may still affect compliance and data quality. These limitations are offset, however, by the study’s strengths: the use of certified trainers, implementation in both clinical and preventive settings, and integration of multi-informant data sources, including parent, teacher, and child assessments.

Ultimately, the Dino Study contributes to the emerging movement toward precision prevention in child mental health care. By capturing day-to-day changes and individual differences in responsiveness, this study may help identify subgroups of children for whom structured interventions are especially effective. In doing so, it moves the field closer to personalized, data-informed approaches that respect the complexity of child development and the diversity of family contexts.

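### For the primary outcomes, the claim that FIML minimizes attrition bias rests on an unstated assumption, and the H1 models as described use nothing observed after T1 for a child without T2

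*Protocol article*

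**What the plan says.** All points are from the protocol article.

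- **Statistical analysis:** "Missing data will be handled using full information maximum likelihood estimation within Latent Change Score (LCS) and multilevel models, minimizing bias due to attrition". No assumption is attached. The only dropout-related sensitivity analysis named is an intention-to-treat analysis of everyone randomized.
- **Study design:** the primary outcomes have two waves, "with T2 scheduled 19 weeks after T1".
- **Hypothesis 1:** "LCS models will be estimated in Mplus for each primary outcome domain"; "Outcomes will be analyzed separately for parent-reported, teacher-reported, and child-assessed measures"; "Intervention condition will be tested as a predictor of pre-to-post change".
- **Preliminary analyses:** the only other variables said to enter are baseline ones: "Any baseline differences that reach statistical significance will be included as covariates in subsequent models".
- **Hypotheses 2 and 3:** the diary is analysed here, in multilevel time-series models. The Power analysis section counts up to 140 diary days per family over 20 weeks.
- **Power analysis and Discussion:** attrition is expected. The sample of 120 is justified partly by it, and the Discussion concedes that "the potential burden on families may still affect compliance and data quality".

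**The concern.** Full information maximum likelihood uses whatever is in the model. In a two-wave model with arm as predictor, nothing observed between T1 and T2 is in it. For a child who leaves, the missing T2 is in effect predicted from T1, arm and any added baseline covariate, using the relation seen in children who stayed.

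That prediction is right on average only if leaving is unrelated to how the child did after T1, given those variables. There is reason to doubt this here. Parents are told their arm after baseline, and Table 1 lists masking of the outcome assessor only. One arm attends 18 weekly sessions of about two hours, while the other waits with access to usual care. Reasons for leaving may therefore differ by arm and follow the child's progress. If poor responders leave the intervention arm, the primary effect is overstated. The intention-to-treat analysis includes everyone randomized, but as described it does not vary the missing-data assumption, so it would not show the problem.

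The trial also records the child's negative affect and behavior problems every evening after T1. This is the kind of information that could make missing-at-random more credible.

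**Working it through.** **The plan's own figures.** The article gives no dropout rate and no figure for attrition bias, so there is none to reproduce. Its sample sizes (64 and 26 per group for d = 0.5 and 0.8) do reproduce with a two-sided t-test, but they do not bear on this point.

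**Diary data left out of H1.** A family leaving after diary week 5, 10 or 15 could have supplied up to 7 × 5 = 35, 7 × 10 = 70 or 7 × 15 = 105 of the 140 days.

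**Model for the size of bias.** Every value here is an assumption.

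- T2 = 0.7·T1 + 0.714·e − 0.5·arm, lower being better; 0.714 = √(1 − 0.7²). The true effect is 0.50 SD.
- The diary course D is independent of T1 and has correlation r = 0.4 to 0.6 with e.
- In the intervention arm a fraction p = 0.10 to 0.25 leaves. The latent tendency to leave has correlation s = 0.5 to 0.9 with D. Control dropout is at random.

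Among children who stay, the mean of D falls by s·λ, with λ = φ(z)/(1 − p) and z the upper p point of the normal distribution. The T1-plus-arm estimate therefore moves by

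shift = 0.714 · r · s · λ.

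| p | λ | s | r | shift | estimate |
|---|---|---|---|---|---|
| 0.10 | 0.1755/0.90 = 0.195 | 0.5 | 0.4 | 0.028 | 0.53 |
| 0.15 | 0.2332/0.85 = 0.274 | 0.7 | 0.4 | 0.055 | 0.55 |
| 0.15 | 0.274 | 0.7 | 0.6 | 0.082 | 0.58 |
| 0.25 | 0.3178/0.75 = 0.424 | 0.9 | 0.6 | 0.163 | 0.66 |

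The range is 0.53 to 0.66 SD, an overstatement of 6% to about 32%. Large-sample simulation agrees.

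**When the bias vanishes.** If the same mechanism and rate act in both arms, both arm means shift equally and the difference stays at 0.50. Simulation confirms this. Bias is also zero if dropout depends only on T1.

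**A second set of assumptions.** With T1–T2 correlation 0.6, logistic dropout with odds doubling per SD of diary worsening in the intervention arm, and partial correlation 0.3 to 0.7:

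- Diary-driven in the intervention arm only, 20% dropout in each arm: bias 0.03 to 0.07 SD.
- Same mechanism in both arms, 30% against 10% dropout: 0.03 to 0.07 SD.
- Mechanism in opposite directions in the two arms: up to 0.14 SD, about 29% of 0.50.

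**What auxiliaries would achieve.** If dropout depends on D and D is measured without error, adding D removes the bias, but that follows from the assumption. Two less favourable cases under the first model:

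- *Diary summary with reliability 0.5.* The remaining shift is the original divided by (1 + v), where v is the variance of D among those who stay. In the worst case v = 0.623, so 0.163/1.623 = 0.10 and the estimate is 0.60. Over the grid it is 0.51 to 0.60.
- *Dropout driven by the T2 residual itself.* In the worst case (p = 0.25, s = 0.9) the T1-only shift is 0.714 × 0.9 × 0.424 = 0.272. With the auxiliary it is multiplied by (1 − r²)/(1 − r² + r²v). For r = 0.4 that is 0.84/(0.84 + 0.16 × 0.623) = 0.894, leaving 0.243 and an estimate of 0.74. In the second model, bias falls only from 0.21 to 0.16 SD.

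In both cases the auxiliary reduced the bias.

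**The case against.** The strongest reply is that this is an omission from a condensed article. Auxiliary variables and the missing-at-random statement commonly stand in an analysis plan, and none is shown. Nothing in the article forbids auxiliaries, and its list of sensitivity analyses is open-ended. This stands as far as it goes: the text does not show that auxiliaries will be left out. The point survives because the article prints an unqualified claim, and the method it describes for H1 does not support that claim.

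Three stronger readings are tempting, but the document does not bear them out.

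- *The diary is ignored.* It is not. The quoted sentence also covers the multilevel models, where a withdrawing family's diary is used for H2 and H3. The gap is confined to H1.
- *A dropout is represented by one T1 score and arm alone.* Covariates may enter through Preliminary analyses, and parent-reported externalizing behavior has two instruments (CBCL and ECBI), so more than one T1 indicator is possible. What is absent is post-T1 information.
- *A family that stops sessions or the diary loses its T2.* The consent wording, that participants "may withdraw from the study at any time without consequence", does not say so. Data collection and procedures pays for the posttest separately from each diary entry, and the intention-to-treat analysis covers everyone regardless of adherence.

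It is also fair to say that the bias is conditional, that it is zero under some plausible mechanisms, and that no rate or correlation above comes from the document.

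**Conclusion.** The point holds for the primary analyses, as a claim that is not supported as written. As described, H1 rests on missingness at random given T1, arm and any selected baseline covariate, and the article does not state that assumption. If dropout follows the child's later course differently in the two arms, or follows it alike but at different rates, the effect is misstated. Under the assumed values with intervention-arm selection only, a true 0.50 SD appears as 0.53 to 0.66 SD; the upper end needs 25% dropout, selection 0.9 and correlation 0.6 together. With equal mechanism and rate in both arms there is no bias.

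A reader might infer that the primary estimate will be biased, or that adding the diary would cure it. Neither follows: the first depends on a dropout pattern not yet known, and the second on the diary carrying the whole reason for leaving. This is a cheap improvement, not a fatal flaw.

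**What to change.** In Statistical analysis and Hypothesis 1:

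1. Prespecify a short set of auxiliary variables for the H1 models: the diary level of negative affect and of behavior problems, summarized over fixed windows so that children who leave and children who stay are comparable, and the other informant's score where the domain has one. That is externalizing behavior, social competence and executive functioning; language, emotional understanding and problem solving have a single source. Sessions attended would not serve, being undefined in the control arm.
2. Replace the statement that bias is minimized with the assumption made: T2 is missing at random given the variables named in the model.
3. Add a delta-adjusted or pattern-mixture sensitivity analysis that lets unobserved T2 values be worse than predicted, separately by arm, because the auxiliaries may leave bias behind.

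The cost is a few sentences and some extra model code, with no new data collection. The downside is that with 120 children the auxiliary set must stay short to avoid convergence problems.

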#### Preliminary analyses.

To evaluate baseline equivalence between the intervention and control groups, independent samples t-tests (or Mann–Whitney U tests for non-normally distributed variables) will be conducted on demographic characteristics, baseline parenting behavior, and child behavioral outcomes. Any baseline differences that reach statistical significance will be included as covariates in subsequent models.

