#### Parent-reported outcomes.

***Parenting behavior (Explanatory outcome; RQ1).*** Parenting practices will be measured using the Parenting Practices Interview (PPI) [38]. The PPI includes 73 items rated on a 6-point Likert scale (1 = “never” to 6 = “always”) and covers domains such as positive involvement, inconsistent discipline, and harshness. A sample item is: “When your child misbehaves, how often do you give up trying to discipline him/her?”. Subscale scores will be used to explore potential changes in parenting behavior. Although parents are not enrolled in a formal parenting program, those whose children receive the Dinosaur intervention are indirectly exposed to parenting principles from the IY program. Through weekly letters, reading assignments, and homework exercises derived from the parent book used in the IY parent training, caregivers are encouraged to apply positive parenting strategies at home. The PPI was specifically developed to assess parenting behaviors targeted by the IY parent intervention

***Child externalizing behavior (Primary outcome; RQ1).*** The Child Behavior Checklist (CBCL) will be used to assess children’s behavioral and emotional problems from the parent’s perspective [39]. The CBCL includes 113 items rated on a 3-point scale (0 = “not true”, 1 = “somewhat true”, 2 = “very true”). The Externalizing Problems composite will serve as the primary indicator of behavioral change. To complement this, the Eyberg Child Behavior Inventory (ECBI) will be administered [40]. The ECBI consists of 36 items (e.g., “Refuses to go to bed”) rated for both frequency and problem severity.

***Child social behavior (Primary outcome; RQ1).*** Social competence will be measured using the Social Competence Scale – Parent version (P-COMP) [41]. This 12-item scale uses a 5-point Likert format (1 = “not at all” to 5 = “very well”) to evaluate skills like cooperation, self-control, and empathy. A sample item is: “How well does your child get along with other children?”.

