***Executive functioning (Primary outcome; RQ1)***. Parents will complete the Behavior Rating Inventory of Executive Function, Second Edition– Parent form (BRIEF-2) [42,43]. This version includes 60 items rated on a 3-point Likert scale (1 = “never”, 2 = “sometimes”, 3 = “often”) and assesses executive functioning in daily life at home. A sample item is: “Has trouble remembering things, even for a few minutes.” The Global Executive Composite (GEC) score will be used at the primary outcome. The BRIEF-2 has demonstrated strong psychometric properties in both clinical and normative samples [44].

***Child language behavior (Primary outcome; RQ1).*** The Children’s Communication Checklist – Second Edition, Dutch version (CCC-2-NL) [45,46] will be used to assess the child’s communicative/language functioning from the perspective of the parent or caregiver. The CCC-2-NL consists of 70 items covering structural language skills (such as syntax and semantics) as well as pragmatic aspects of communication (e.g., inappropriate initiation, use of context, nonverbal communication). Items are rated on a 4-point scale (0 = “less than once a week or never” to 3 = “several times a day or always”), providing standardized composite scores to identify potential communication difficulties. The General Communication Composite (GCC) derived from the CCC-2-NL will serve as the primary indicator of change in child communicative behavior.

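### Covariates for the outcome models are chosen by baseline significance tests rather than fixed in advance; the claim that the change-score models remove measurement error holds only if each model has more than one indicator per wave.

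*Protocol article*

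**What the plan says.** Under Preliminary analyses, t-tests or Mann–Whitney tests "will be conducted on demographic characteristics, baseline parenting behavior, and child behavioral outcomes". The rule that follows is: "Any baseline differences that reach statistical significance will be included as covariates in subsequent models". This is the only covariate rule in the article. Age, gender and severity at baseline appear in the opening paragraph of Statistical analysis, but as subgroup moderators, not as covariates for the main models.

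Under Hypothesis 1, an LCS model is fitted for each primary outcome domain, separately by informant. "Intervention condition will be tested as a predictor of pre-to-post change" is all that is said about the group effect. The section also states: "LCS models estimate change over time using latent difference scores, thereby distinguishing true change from measurement error".

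Several parent-reported outcomes are defined by one composite. For the CBCL: "The Externalizing Problems composite will serve as the primary indicator of behavioral change". For the BRIEF-2: "The Global Executive Composite (GEC) score will be used at the primary outcome". For the CCC-2-NL: "The General Communication Composite (GCC) derived from the CCC-2-NL will serve as the primary indicator of change". For externalizing behavior there is also a second parent instrument: "To complement this, the Eyberg Child Behavior Inventory (ECBI) will be administered".

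**The concern.** In a randomised trial a baseline test asks a question whose answer is known: if allocation was sound, the difference arose by chance. A p-value filter therefore admits variables for being unbalanced, not for being prognostic. A strong predictor with a moderate imbalance stays out, and a weak one with a chance imbalance comes in. The covariate set, and with it the estimate and standard error, is unknown until the data are seen.

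The variable that matters most is the outcome's own T1 score. If it enters only when significant, most of the precision available from it is given up. The trial has little to spare: the Power analysis section requires 64 per group for d = 0.5, and 60 per arm are planned before attrition.

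The second, conditional matter is the measurement-error statement. It is true of an LCS model with several indicators per wave. It is not true of a two-wave model with one composite per wave.

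**Working it through.** **1. The plan's own figures.** Two-sample t-test, two-sided alpha 0.05, power 0.80, 1:1 (Power analysis section; sidedness is not stated, but two-sided reproduces). For d = 0.5 the solution is 63.77, so 64 per group; for d = 0.8 it is 25.52, so 26. Both match. At the planned 60 per arm, power for d = 0.5 without baseline adjustment of any kind is 0.775.

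**2. Chance of a data-driven covariate.** P(at least one of k independent tests has p < 0.05) = 1 − 0.95^k.
- k = 5: 0.23
- k = 10: 0.40
- k = 20: 0.64

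The article does not give k, so it is an assumption. The outcome sections list about 11 child scores (CBCL, two ECBI ratings, P-COMP, two BRIEF-2 composites, CCC-2-NL, TRF, T-COMP, two Wally tests), with parenting subscales and demographics on top. Correlated scales would lower these probabilities.

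**3. Behaviour of the rule.** Simulation of 8,000 trials per scenario, 60 per arm, condition predicting the raw change score, T1 added only if its own baseline t-test gives p < 0.05. The pre-post correlation r is not in the article; 0.5 and 0.7 are assumed.
- T1 is selected in 4.6% to 5.5% of trials.
- The mean estimate is 0.497 to 0.498 when the true effect is 0.5, so there is no bias.
- Rejection under no effect is 0.045 (r = 0.5) and 0.049 (r = 0.7), so there is no type I inflation.
- SD of the estimate at r = 0.5: 0.183–0.184 never adjusted, 0.177–0.178 under the rule, 0.159 always adjusted. The rule recovers little of the gain.

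**4. Power, if the group effect is a raw change contrast.** With unit outcome SD, residual variance is 2(1 − r) for raw change and 1 − r² with T1 in the model. Their ratio is (1 + r)/2.

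| r (assumed) | Variance, raw change | Variance, T1 included | Power, raw change | Power, T1 included |
|---|---|---|---|---|
| 0.3 | 1.40 | 0.91 | 0.63 | 0.81 |
| 0.5 | 1.00 | 0.75 | 0.775 | 0.88 |
| 0.7 | 0.60 | 0.51 | 0.94 | 0.97 |
| 0.8 | 0.40 | 0.36 | 0.990 | 0.995 |

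(60 per arm, d = 0.5, two-sided 0.05.) Under the selection rule, simulated power is 0.78 at r = 0.5 and 0.94 at r = 0.7, close to the raw change column.

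**5. Identification of a single-indicator LCS model.** Two waves of one score give 3 variance–covariance moments (two variances, one covariance). The model needs the variance of true T1, the variance of true change and their covariance (3), plus two error variances: 5 unknowns. The error variances must be fixed. If they are fixed at zero, the latent change is the observed difference. The reliability of that difference is (rel − r)/(1 − r). With assumed reliability 0.80 it is 0.60 at r = 0.5 and 0.33 at r = 0.7; with 0.90 it is 0.80 and 0.67. The rest of the change variance is noise.

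**The case against.** **T1 may already be in the model.** A reader might infer that the plan leaves T1 unadjusted. The article does not say so. An LCS model contains the baseline score. If change is regressed on it, or covaries with it while T1 is not regressed on condition, the group effect is essentially the baseline-adjusted one. If T1 is also regressed on condition, it is the raw change difference. Listing child behavioral outcomes among the variables screened for significance hints that adjustment is conditional, but does not prove it. This stands: the power loss in step 4 applies to one of two readings.

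**The rule might be thought to bias the result.** It does not (step 3). An imbalance just short of significance, 1.96 × √(2/60) = 0.36 SD, would move a raw change contrast by 0.36 × (1 − 0.6) = 0.14 SD at r = 0.6. That is a shift given a particular chance imbalance, not bias over repeated trials.

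**The measurement-error statement might be called false.** That goes too far. The article never says that one composite per wave is the sole indicator. The ECBI complements the CBCL, items or subscales could serve as indicators, and the measurement model may sit in a fuller document. The composites named make the single-indicator reading plausible, not established.

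**Nor can one infer that a core aim is compromised.** The study aim ties individual variability in response mainly to the daily diary, and nothing says that the LCS change variance will be read as true heterogeneity.

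None of this rescues the covariate rule, which is stated outright.

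**Conclusion.** The covariate rule should be replaced. It makes the analysis model depend on chance and selects on imbalance instead of prognostic value. That conclusion needs no assumption beyond sound randomisation; the 23%, 40% and 64% figures assume the number and independence of tests.

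The cost is precision and pre-specification, not validity. The power loss is about 10 percentage points at r = 0.5 (0.775 against 0.88) and about 3 at r = 0.7 (0.94 against 0.97). It arises only if the LCS group effect is not already conditional on T1, which the article leaves open.

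The measurement-error point is conditional. If each model uses only the single composite named for its outcome at two waves, the statement does not hold; with several indicators per wave it can.

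**What to change.** 1. Delete the significance-test rule. Keep the baseline comparison as a descriptive table.
2. In every Hypothesis 1 model, condition change on the same outcome's T1 score and include age, sex and recruitment setting (clinical or preventive), whatever the observed imbalance. State how T1 enters the LCS model, so that the group effect is clearly the baseline-adjusted one.
3. State the indicators of each LCS model. If only one composite per wave is used, take one of three routes: use several indicators with invariance constraints across waves; fix the error variance at (1 − reliability) × observed variance from a known reliability; or withdraw the measurement-error statement and do not read the change variance as true heterogeneity.

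Cost: a change of analysis wording. The covariates are collected or known at enrolment. With 120 children and a two-level setting variable, the fixed set uses at most four degrees of freedom (residual 120 − 2 = 118 falls to 114), or three if T1 is already in the model. Several indicators would make a larger model for 120 children. Fixing the error variance makes the result depend on the reliability chosen, so a range should be shown.
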